#### WHO tunnel test

Each site will perform tunnel tests independently on each ITN that did not meet WHO efficacy criteria (i.e., ≥ 95% KD_60_ or ≥ 80% M_24_) in the cone test against the susceptible strains of mosquitoes, only one out of four net pieces will be selected for the tunnel test. This is the piece that gave mortality closest to the average mortality in the cone test of the four pieces (i.e., average for that net). The selected piece will be fixed in the tunnel for testing. One tunnel with untreated netting will be used as a negative control. Fifty non-blood fed female susceptible *Anopheles* mosquitoes aged 5–8 days sugar starved for 6–8 h will be released in a tunnel (square section 25 cm × 25 cm) made of glass, 60 cm in length [8]. For pyrethroid only nets, susceptible mosquitoes will be used, while for PBO nets, both susceptible and resistant strains will be used.

At one-third of the length, the netting sample is fixed, with the surface of netting available to mosquitoes of 400 cm^2^ (20 cm × 20 cm) with nine holes each 1 cm in diameter: one hole is located at the centre of the square; the other eight are equidistant and located at 5 cm from the border. In the shorter section of the tunnel, a small rabbit, which will be restrained and unable to move but available to mosquitoes, will be placed as bait. To minimize discomfort to the rabbits, all applicable experimental animal welfare procedures will be adhered to following specific country regulations. In the cage at the end of the longer section of the tunnel, 50 female mosquitoes [52] will be introduced at 18:00. The following morning from 09:00, the mosquitoes will be removed using a mouth aspirator and counted separately from each section of the tunnel and mortality and blood-feeding rates will be recorded. During the test, ambient conditions will be maintained at 27 °C ± 5 °C and 60–100% relative humidity. Acceptable feeding success and mortality in controls will be ≥ 50% and ≤ 10%, respectively.

#### Chemical residual analysis

The residual chemical concentration will be estimated for all products at baseline and after every 12 months using nets allocated in B-list. At baseline, five net pieces (25 cm × 25 cm) will be cut from 30 different mosquito nets (position 1 to 5 of each net) per product and at 12, 24 and 36 months, four net pieces will be cut from position 2 to 5 from the nets sampled for bio-efficacy testing of each product [8]. These pieces will be rolled up and placed in a labelled aluminium foil and stored at 4 °C until they are shipped for chemical analysis following CIPAC methods as described in the WHO specifications for each ITN to check if the chemical concentrations are within the tolerance limit as per the manufacturer’s specifications [Tsara Boost: 333/LN/(M)/3, 33/LN/(M)/3 [53]; Veeralin: 454/LN/(M)/3, 33/LN/(M)/3 [54]; Olyset Plus 331/LN/(M)/3, 33/LN/(M)/3 [55]; MAGNet 454/LN/(M)/3] and within range after operational use [56].

#### Mortality and blood-feeding for PBO ITNs in Ifakara Ambient Chamber Test

Whole ITNs returned from the field at 12 and 24 months for bio-efficacy testing in Tanzania and unwashed and 20 times laboratory washed nets of each product will be evaluated in 18 chambers of the Ifakara Ambient Chamber Test (IACT) in Tanzania [41, 57]. Overall, the 18-arm study will include 4 arms of field-aged nets, 4 arms of unwashed and 4 arms of twenty-times laboratory-washed nets of the brands: Olyset® Plus, Veeralin®, Tsara® Boost and MAGNet® and two untreated nets (negative controls) and two additional positive control nets: PermaNet® 3.0 and standard Olyset® nets both unwashed and twenty-times washed. Unwashed, twenty-times washed nets, positive and negative control nets will be deliberately holed with six holes (4 × 4 cm) as per guidance [8]. Eighteen volunteers will rotate sequentially among the 18 chambers of the IACT nightly based on a prepared roster to allow equal sleeping under nets per product among volunteers. Each chamber of the IACT will have a bed net frame over which the ITN will be draped and a foam mattress upon which one volunteer will sleep. The study will run for seventy-two experimental nights per time point (12 months and 24 months). After 54 experimental nights, each unwashed, 20 times washed nets and positive controls will be replaced with field aged nets for the last 18 nights from the IACT to allow four field aged nets of each product tested for each of the remaining 18 experimental nights, leading to 126 replicates per field-aged product in total. This is done to allow a sufficient sample size for the non-inferiority comparison of field aged nets against Olyset® Plus field-aged net.

IACT allows the testing of multiple strains of mosquitoes at the same time. To understand the bio-efficacy of ITNs on the susceptible and resistant mosquitoes, fifteen nulliparous, sugar starved for 6–8 h, female susceptible *An. gambiae* s.s. Ifakara strain and a resistant *An. arabiensis* Kingani strain mosquitoes will be released at 21.00 h in each of the compartments occupied by one volunteer sleeping under one of the tests ITNs or a negative control net. These species are morphologically identical; thus, one strain will be marked with a fluorescent dye that does not affect their survival or behaviour [58]. At 06.00 h, each volunteer will collect mosquitoes inside the compartment using a mouth aspirator in paper cups. Recaptured mosquitoes will be sorted by species and recorded as fed alive, fed dead, unfed alive and unfed dead, then will be provided with 10% sucrose solution, and held under standard laboratory conditions to assess delayed mortality at 24-h.

### Sample size

#### The sample size for the ITN surveys

The sample size was calculated based on the primary outcome measure of net attrition together with additional nets for the bio-efficacy components. Assuming an average of 2.7 nets per household and a coefficient of variation of 0.25, the formula on page 110 of Hayes and Moulton [59] gives a sample size of 678 households per arm to detect the difference in attrition between two products assuming 3-year attrition rates of 47.5% and 52.5% with 80% power. An additional 260 households for bio-efficacy, chemical analysis and IACT have been added to 678 making a total number of 938 households. Since the median lifespan of ITNs products from durability studies in Tanzania is less than 3 years [29, 60, 61], a 41% loss to follow-up of households is assumed making addition of 657 households to the 938 households. The final total number of households that will be recruited at baseline per product per country is 1595. With an average of 2.7 nets per household [62], the total number of ITNs required per product per country will be 4521 including 5% for error due to poor quality or nets with open seam prior to distribution, Table 5.

**Table 5 Tab5:** Description of the numbers of ITNs distributed in the study area

Households for longitudinal attrition and fabric integrity monitoring	678
Households for I-ACT, cone bioassay and chemical testing	260
Unadjusted total households per product per country	938
Loss to follow up households	657
Adjusted total households per product per country	1595
The average number of ITNs per household per product	2.7
Total ITNs per product	4305
5% error and nets for replacement	215
Total ITNS required for each product per country	4521

The same net used in the IACT will be used for cone bioassay and chemical testing

#### The sample size for the entomological outcomes in the IACT

Simulation was used to determine the sample size for the bio-efficacy testing of ITNs in the IACT. Each PBO net product will be assessed for non-inferiority against Olyset® Plus on mortality at 24 h. Each product will have sixty nets some tested more than one times for 72 nights with 15 mosquitoes per strain per chamber per night. From a previous study (author, pers.commun.), the variation between individual field-aged nets per product was assumed at a standard deviation of 0.1 and between chamber-nights at 0.15, both on the log-odds scale. Assuming mortality of 70% for the PBO nets and Olyset Plus, 1000 simulation trials were conducted to assess non-inferiority for each trial and the power estimated by the proportion of trials that showed non-inferiority where the product was indeed non-inferior, was over 80%.

To assess the equivalence of field nets to 20-times washed nets on mortality, each product consisting of sixty replicates of field-aged nets as well as four replicates of twenty times laboratory washed and unwashed nets will be tested 54 times (three rounds with 18 replicates each). Assuming 70% mortality for each product of field and washed nets, and assuming 0.1 standard deviation between individual replicate nets per product and a chamber-night standard deviation of 0.15 on the log-odds scale, using 15 mosquitoes per strain per chamber per night, the study is powered at 80%.

#### Samples size for chemical analysis

The baseline quality assurance of the ITNs used in the durability trial is conducted by chemical analysis and biological efficacy testing. A problem with the batch is detected if one or more of the sampled nets fails to meet the acceptance criteria. Since the same batch of nets are tested in three study countries, 10 ITNs are evaluated per site to give a total sample size of 30 ITNs tested at baseline as per WHO guidelines [8]. During each of the subsequent survey time point, 30 net samples will be sampled for chemical analysis as per WHO guidelines [8].

### Data management

Field data will be collected using electronic data capture format in Open Data Kit (ODK) Collect. The data will be sent to the secure server located at Ifakara Health Institute in Tanzania. Cleaned data sets will be returned to CSRS and NIMR India. The information from the baseline questionnaire will be linked to the follow-up surveys using the unique household and country identification number as well as unique net identification numbers. Data collected on paper forms in the laboratory and in the IACT will be entered in excel using double-entry to facilitate cross-referencing and validation. The cleaned excel file of the data will be uploaded to the IHI server. Access to the data on the server will be limited to the data manager.

### Data analysis

All data analyses will be conducted using STATA software (Stata Corp LLC, College Station TX, USA). The durability outcomes; attrition, fabric integrity, bio-efficacy and insecticide content will be estimated (Table 4). These outcomes will be estimated for each net product by survey period and country. A pooled estimate from three countries will also be presented, if appropriate.

The non-inferiority of Veeralin® and Tsara® Boost nets to Olyset® Plus will be carried out using logistic regression for the binary outcome of mosquito mortality with ITN product, compartment, volunteer and day as covariates. A random effect for chamber-night will be included. The 95% confidence interval for the estimated odds ratio for the effect of Tsara Boost® and Veeralin® compared to Olyset® Plus will be presented. Non-inferiority is shown if the confidence interval excludes an unacceptably worse performance. The bound of the margin of non-inferiority for mortality will be set at 0.7. If the lower bound of the confidence interval for the effect of the candidate net compared to Olyset® Plus is greater than 0.7, then we will conclude that the net product is non-inferior [36].

The utility of washed nets as a proxy for field nets will be assessed on the mortality and blood-feeding inhibition endpoints using logistic regression. The estimated odds ratios for the effect of washed nets compared to the negative control, and field-aged nets compared to the negative control will be presented. The ratio of these odds ratios will be estimated along with the 95% confidence interval using interaction terms in the logistic regression model.

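### The IACT analysis names no random effect for the individual net, although the power calculation assumes one, so intervals for comparisons involving the four-net laboratory arms come out about 8–14% too narrow

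*Protocol article*

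**What the plan says.** The Data analysis section of the protocol article gives the non-inferiority model as logistic regression for mosquito mortality "with ITN product, compartment, volunteer and day as covariates", and adds: "A random effect for chamber-night will be included". Net identity does not appear. The next paragraph, on washed nets as a proxy for field nets, estimates a ratio of odds ratios with a 95% confidence interval "using interaction terms in the logistic regression model" and names no random effect.

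The section on the sample size for the entomological outcomes in the IACT uses two variance components. For non-inferiority, "the variation between individual field-aged nets per product was assumed at a standard deviation of 0.1 and between chamber-nights at 0.15". For equivalence the power statement is made "assuming 0.1 standard deviation between individual replicate nets per product and a chamber-night standard deviation of 0.15 on the log-odds scale". On replication it says "four replicates of twenty times laboratory washed and unwashed nets will be tested 54 times", and for the field-aged nets "Each product will have sixty nets some tested more than one times for 72 nights".

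The section describing the IACT procedure gives one chamber per laboratory arm for 54 nights. Field-aged nets then replace the laboratory arms for 18 nights, which brings each field-aged product to 126 replicates.

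**The concern.** The design recognises that nets of one product differ, but the stated analysis has no term for that difference. Each test is one net in one chamber on one night, so the chamber-night effect is specific to the test. It cannot carry the correlation between different nights on the same net. Compartment, volunteer and day cannot carry it either.

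This matters where few nets are used many times. A washed arm has 54 tests but only four nets, and between-net variation averages out over the four. The comparison of 20-times washed with field-aged nets is secondary objective vi, and the Discussion says the study will examine whether the 20-wash proxy is acceptable. That is a statement about products, so net-to-net variation belongs in its error bars.

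**Working it through.** **Inputs from the protocol article.** Mortality 70% in both arms; 15 mosquitoes per strain per chamber-night; chamber-night SD 0.15; net SD 0.1; non-inferiority margin 0.7 for the odds ratio; washed or unwashed arm 4 nets and 54 tests; field-aged arm 60 nets and 126 tests (54 + 4 × 18). Because the equivalence paragraph speaks of 54 tests, a field arm of 54 tests on 54 nets is also shown. I read the 54 tests as the total per arm, which fits one chamber for 54 nights.

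**Formulas.** Variance of an arm's log-odds with the net level included:

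V = 1/(tests × 15 × 0.7 × 0.3) + 0.15²/tests + 0.1²/nets

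With a chamber-night effect only, net variance is absorbed as if it were fresh in every test, so the last term becomes 0.1²/tests. The SE of a contrast is the square root of the two arms' summed variances. True coverage of the nominal 95% interval is 2Φ(1.96 × SE without net / SE with net) − 1. In the ratio of odds ratios the shared negative control cancels, so this ratio is the washed-versus-field odds ratio.

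**The plan's own power.** Non-inferiority power is Φ(ln(1/0.7)/SE − 1.96), with ln(1/0.7) = 0.357. For 126 tests on 60 nets the SE is 0.0757 and power is 99.7%. For 72 tests on 60 nets it is 95.0%, and for 54 tests on 54 nets 88.0%. All agree with the stated figure of over 80%. The 80% for equivalence cannot be strictly reproduced, since the article gives no equivalence margin. With an assumed margin of 0.7 to 1/0.7 and net variance included, power is 82.1% (126 field tests, 95% interval), 78.5% (54 field tests, 90% interval) or 64.5% (54 field tests, 95% interval).

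**Arm variances at net SD 0.1.**
- Laboratory arm, with net level: 0.00588 + 0.00042 + 0.01/4 = 0.00880. Chamber-night only: 0.00588 + 0.00042 + 0.01/54 = 0.00648.
- Field arm (126 tests, 60 nets), with net level: 0.00252 + 0.00018 + 0.01/60 = 0.00286. Chamber-night only: 0.00252 + 0.00018 + 0.01/126 = 0.00278.
- Field arm (54 tests, 54 nets): 0.00648 either way.

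| Contrast | SE with net | SE chamber-night only | Too narrow by | True coverage |
|---|---|---|---|---|
| Washed v field (126/60) | 0.108 | 0.096 | 11% | about 92% |
| Washed v field (54/54) | 0.124 | 0.114 | 8% | about 93% |
| Washed v unwashed | 0.133 | 0.114 | 14% | about 91% |
| Field v field, non-inferiority (126/60) | 0.0757 | 0.0745 | 1.5% | 94.6% |

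For washed versus field (126/60), one-sided error at a margin would be about 4.0% instead of 2.5%.

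**Simulation check.** Fitting the chamber-night-only model to 1000 simulated trials per scenario gave, for washed versus field (126/60), coverage of 95.2% at net SD 0 and 92.5% at net SD 0.1 (mean SE 0.097 against an empirical SD of 0.106). With 54/54 field tests and SD 0.1 it gave 94.1%, somewhat above the formula's 93%; Monte Carlo error is about 0.7 points.

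**Sensitivity (assumed values, not in the protocol).** For washed versus field (126/60), net SD 0.2 gives coverage of about 84% and 0.3 about 75%; with 54/54, about 87% and 80%. If each laboratory net were tested 54 times (216 tests per arm), the interval against 126 field tests would be about 20% too narrow at SD 0.1.

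**The case against.** The sentence naming the chamber-night effect belongs to the non-inferiority analysis, the one IACT analysis with a stated margin and decision rule. There, 60 nets with about two tests each leave almost no distortion. A reader might infer that every IACT interval, and so the non-inferiority verdict, is materially too narrow. The figures do not support that: 1.5% at the plan's SD, with power of 99.7%. This part of the objection stands.

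A reader might also infer that the washed-net analysis will have no random effect at all. On that reading the binomial-only SE is √(0.00588 + 0.00252) = 0.092 against 0.108, and coverage about 90%. The paragraph is brief, however, and the article uses logistic regression as shorthand elsewhere: Table 4 does so while its footnote c adds a household random effect. Silence does not prove omission, so the headline figures assume a chamber-night effect is present. Even then the net level appears nowhere in the IACT analysis, and the household effect does not cover repeat tests of a laboratory-washed net.

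Coverage of 75–87% is tempting to cite but needs net SDs that the protocol does not give.

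Finally, washed versus field is a secondary objective reported as an estimate with an interval and no stated decision rule. A narrowing of about 10% therefore overturns no prespecified decision. That limits the severity, but the reported interval would still be wrong.

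**Conclusion.** The point holds for comparisons that involve the laboratory arms and should be fixed. The plan's power calculation and its stated analysis disagree on the variance structure. At the plan's own net SD of 0.1, intervals are too narrow by about 8–11% for washed versus field, depending on whether 54 or 126 field tests enter, and by about 14% for washed versus unwashed. This rests on 54 tests in total per laboratory arm, 70% mortality, and a net SD of 0.1 applying to washed and unwashed nets as well as field-aged ones. The error is moderate under these inputs and severe only if nets vary more than the plan assumes. The non-inferiority comparison of field-aged nets is not put in doubt.

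**What to change.** In the Data analysis section, add a random intercept for individual net beside chamber-night in both IACT models, above all in the model for the washed-versus-field ratio of odds ratios. State a small-sample degrees-of-freedom correction for arms with four nets. Confirm that the identity of each washed and unwashed net is recorded on each test night: the article describes unique codes for nets distributed to households and does not say the same for laboratory nets.

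If those identities are recorded, this needs no new data. Intervals for the washed and unwashed comparisons become wider. From the SEs alone, washed versus field (126/60) widens by 0.108/0.096, about 12%, and the small-sample correction adds to that. Applying a t multiplier on 3 degrees of freedom (3.18 instead of 1.96) to the whole contrast would overcorrect, because the four laboratory nets contribute only 0.0025 of the total variance of 0.0117, about 21%. The method for the degrees of freedom should therefore be named. Spreading the 54 tests over more laboratory nets would also help, but it changes the design of a study already under way and is not needed for this correction.

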## Discussion

This study is the first large-scale prospective household randomized controlled trial of PBO ITNs in three different countries simultaneously. It will allow a pooled estimate of ITN durability from three countries, enabling precise estimates of product performance over time.

In a cluster randomized trial that assessed the effectiveness of Olyset® plus, there was a high washout of PBO concentration within 21 months of use under operational conditions [19] and more than 97% washout after 3 years [63]. Similarly, Olyset® Plus lost more than 87% of PBO concentration after 3 years in Kenya [64]. In Uganda, more than 55% of PBO concentration in Olyset® Plus was washed out within 25 month [65]. These publications highlight the importance of describing the estimated period of performance of PBO ITNs in different contexts. This study will report the persistence of PBO and pyrethroid concentrations in Olyset® Plus, Veeralin®, and Tsara Boost® beside pyrethroid concentration in MAGNet® for the period of 3 years of use in the field in three locations. It will also monitor the added value of PBO against resistant strains of mosquitoes over time as recommended for durability monitoring of products designed to kill pyrethroid-resistant malaria vectors [66].

PBO ITNs including Veeralin® and Tsara® Boost are currently recommended as pyrethroid only ITNs [67, 68] and are required to demonstrate non-inferiority using 24-h mortality and feeding inhibition endpoints compared to the first-in-class Olyset® Plus [69]. This study will measure the non-inferiority of Veeralin® and Tsara® Boost compared to the Olyset® Plus, collected from the field operational settings i.e. the non-inferiority as part of product durability evaluation. Currently, twenty times washed, deliberately holed ITN is used as a reasonable proxy for a field aged net. This study will explore whether this assumption is acceptable, or if it should be revised.

The results of this trial will provide robust and rigorous evidence of the likely replenishment interval, quality and additional bio-efficacy of PBO ITNs compared to pyrethroid only ITNs up to 3 years after the distribution.

## Current study status

This study has finished baseline household data collection and the distribution of ITNs in the study areas in all countries. Currently, follow-up households' data collection and ITNs durability monitoring is ongoing in all study countries. The last follow-up household data collection and ITNs monitoring is expected to end in October 2023.

## Data Availability

Not applicable.

## Abbreviations

CIPAC: Collaborative International Pesticides Analytical Council
GPS: Global positioning system
IACT: Ifakara Ambient Chamber Test
ICF: Informed consent form
IRB: Institutional Review Board
ITNs: Insecticide-treated nets
KD_60_: Knockdown after 60 min
LLINs: Long-lasting insecticidal nets
M_24_: Mortality after 24 h
ODK: Open Data Kit
PBO: Piperonyl-butoxide
pHI: Proportionate hole index
UID: Unique identifiers
WHO: World Health Organization
